## **NON-SPECIFIC EFFECTS OF VACCINES - IN SEARCH OF THE IMMUNOLOGICAL BACKGROUND -**

### **OBJECTIVES**

- General: To investigate the immunological background for the non-specific effects of diphtheria-tetanus-pertussis (DTP) and measles vaccines on child mortality
- Specific: Examine the cytokine responses and possible association with morbidity in a study of DTP vaccinated children who will be randomised to receive a measles vaccine or no vaccine at 4½ months of age. (All children will receive a measles vaccine at 9 months of age).

### **INTRODUCTION / BACKGROUND**

A multitude of epidemiological analyses on vaccination data suggest that basically all the vaccines used in the Expanded Programme on Immunization (EPI) are associated with non-specific effects on child mortality in countries with high child mortality. Bacillus Calmette Guérin (BCG), measles and oral polio (OPV) vaccines are associated with decreased child mortality, while the opposite seems to be the case for DTP and hepatitis B (HBV) vaccines. The background for this phenomenon is virtually unknown, but has been ascribed to stimulation by the vaccine of the immune system rendering the individual either more resistant or more prone to succumbing to the high infectious pressure in these environments.

### **BACKGROUND**

#### *Non-specific effects of vaccines*

The idea of vaccines having non-specific effects was first proposed in 1991 from a study in Senegal, West Africa. It was discovered that children receiving high-titre measles vaccine (HT) at 6 months of age had higher mortality than children who received the standard titre measles vaccine (STD) at 9 months of age. The difference was found only for girls. A study from Haiti confirmed the effect. Since children vaccinated with HT had lower mortality than their equivalents who had not received any measles vaccine, the difference in mortality between recipients of HT vaccine and STD vaccine was explained by a non-specific beneficial effect of the STD measles vaccine rather than a harmful effect of the HT vaccine. The non-specific beneficial effect of STD measles vaccine on child mortality has been reconfirmed in many data-sets.

Also the BCG vaccine is associated with striking effects on child mortality reducing mortality by about 50%. Further, among BCG vaccinated children, having a BCG scar or a positive tuberculin reaction was associated with about 55% lower mortality in the following 12 months than among children who had a negative tuberculin reaction or who did not have a BCG scar.

The effect of OPV is difficult to separate from the effects of BCG and DTP vaccines since OPV is normally given together with these vaccines. There have, though, been some periods without DTP in Bissau due to global shortage of vaccines, and we have compared the case fatality at the hospital for children who received only OPV and children who received both the prescribed OPV and DTP. Children having received OPV had 3-fold lower mortality than children having received both vaccines. Data from an OPV vaccination campaign that took place in Guinea-Bissau also suggested a non-specific beneficial effect for the recipients. Further, studies from Chile and the Soviet Union have suggested that OPV had a beneficial effect on mortality and morbidity.

In contrast, DTP, HBV and inactivated polio vaccine (IPV) seem to exert a non-specific detrimental effect on child mortality, although the findings on DTP were considered controversial by a recent review. Current studies indicate that the negative effect of

DTP may be neutralized by a subsequent measles vaccination. It is striking that all the vaccines with a non-specific beneficial effect are live, whereas the vaccines with an apparently harmful effect are killed. Results from animal studies have shown that attenuated live vaccines tend to induce a Th1 response and offer better protection against severe disease than the corresponding inactivated vaccines, which tend to induce a Th2 response. So far, very few studies have examined whether these effects differ between male and female animals. One study reported that BCG-vaccinated female mice were better protected against malaria parasites than male mice. There is therefore an urgent need to conduct studies that can help uncover the immunology behind the non-specific effects.

### Sex-specific effects

All epidemiological studies carried out so far confirms the observation that non-specific effects are sex-specific. Live vaccines (measles, BCG, OPV) have a beneficial effect that is particularly good for girls whereas inactivated vaccines (DTP, HBV, IPV) have a negative effect for girls. To date, there are no immunological studies which have examined whether routine vaccines affect the immune system differently for boys and girls.

We thus propose to study, in a randomised controlled trial of measles vaccination taking place in Guinea-Bissau, the immunology of non-specific effects of vaccination, and their interaction with sex. Specifically, among children who have received the 3 recommended doses of DTP, we will be able to compare the cytokine and antibody profiles of children who receive an early dose of measles vaccine at 4½ months of age with children who receive no additional vaccine at this age (please refer to methods).

## METHODS

### Study site

The Bandim Health Project (BHP) has a demographic surveillance system in several districts of the capital of Guinea-Bissau, and the current population in these districts is around 80.000. All houses in the area are visited every month to register new pregnancies and births. The BHP visits all children at home every 3 months until the age of three years. Information is collected routinely on breastfeeding patterns, infections, hospitalisation, vaccination status, living with the mother, and ownership of pigs. The people of Bissau are travelling a lot due to extended families living in other parts of the country, cashew harvest, and trade. About 20% of the mothers are travelling at any given time. About 2.600 children are born in the BHP study area each year, and experience shows that we will be able to enrol about 80% of these in a measles vaccine trial i.e. about 2.000 infants per year.

### Measles vaccination trial

We are currently conducting a randomised measles vaccination trial with the following schedule:

|               | Very early two-dose | 9 months one- or two-dose |                |
|---------------|----------------------------|----------------------------------|----------------|
|               | st-EZ               | st-SW or st-EZ     |                |
|               | arm I               | arm II                    | arm III |
| 4½ mo. of age | V ✕                        |                                  |                |
| 9 mo. of age  | V ✕                        | V ✕                              | V ✕            |
| 18 mo. of age |                            | V/nothing ✕                      | V/nothing ✕    |
| 24 mo. of age | ✕                          | ✕                                | ✕              |

V = measles vaccination, ✕ = Blood sampling, st-EZ = standard-titre Edmonston-Zagreb measles vaccine, st-SW = standard titre Schwarz measles vaccine

The aims of the trial are to examine:

- whether the negative effect of the DTP vaccine, which is administered by the EPI-programme at 6, 10 and 14 weeks of age, can be reverted by administration of a measles vaccine 4 weeks after the last DTP vaccination at around 4½ months of age
- whether the standard-titre Edmonston-Zagreb (EZ) vaccine will be suitable for use in a very early two-dose schedule vaccinating at 4½ and 9 months of age, and
- whether the standard titre Schwarz (SW) or standard-titre Edmonston-Zagreb (EZ) measles vaccine will be the best vaccine strain for use in a routine one-dose measles vaccination schedule and a two-dose measles vaccination schedule in terms of antibody response, protection against measles and child survival

Preliminary results, measles vaccination trial

The study was initiated in August 2003, and has currently recruited 2025 children. All routines are working well. A morbidity survey was implemented in August 2004.

It is too early to say anything about relative mortality in the three study arms. However, BHP has for many years registered all paediatric hospitalisations in Bissau which allows us to use hospitalisations as a morbidity outcome. Preliminary data on hospitalisations from the paediatric department in Bissau suggest that as predicted early measles vaccination protects strongly against hospitalisation for measles infection (see Table) but may also be beneficial, at least for girls, in protecting against hospitalisations for other causes. These preliminary results from a randomised trial corroborate our previous observational studies showing measles vaccine to be associated with a low female-male mortality ratio and DTP with a higher female-male ratio.

| Hospitalisations (cases/children at risk) between 1st and 2nd vaccine in two-dose trial |                                            |                                            |                                         |
|----------------------------------------------------------------------------------------------------------------------|--------------------------------------------|--------------------------------------------|-----------------------------------------|
|                                                                                                                      | EZ measles vaccine
at 4½ months | No measles vaccine
at 4½ months | RR (EZ / no
measles vaccine) |
| Hospitalisations for
measles infection                                                                    |                                            |                                            |                                         |
| Male                                                                                                          | 0 (0/333)                                  | 0.01 (10/698)                              | 0 (0-0.94)                              |
| Female                                                                                                        | 0 (0/344)                                  | 0.01 (6/647)                               | 0 (0-1.60)                              |
| All                                                                                                           | 0 (0/677)                                  | 0.01 (16/1345)                             | 0 (0-0.52)                              |
| Hospitalisation for non-
measles infections                                                               |                                            |                                            |                                         |
| Male                                                                                                          | 0.02 (8/333)                               | 0.03 (20/698)                              | 0.84 (0.32-1.99)                        |
| Female                                                                                                        | 0.01 (5/344)                               | 0.04 (29/647)                              | 0.32 (0.10-0.85)                        |
| All                                                                                                           | 0.02 (13/677)                              | 0.04 (49/1345)                             | 0.53 (0.26-0.99)                        |

The proposed study will be conducted as an immunological study performed among a subgroup of the participants in the above study.

Procedures, measles vaccination trial

Newborn infants are identified in the BHP registration system. To make sure that all children have received three doses of DTP before inclusion in the Two-dose trial, we contact the mothers of 6, 10 and 14 weeks old children, and remind them to go to the local health centre to receive the DTP

vaccine. The formal inclusion in the Two-dose trial is at 4½ months of age. During the morning hours field-workers contact the mothers/guardians of the children to be included in the study. The field-workers explain about the study, perform a questionnaire, and obtain verbal consent (please refer to ethical considerations).

In the afternoon, the mothers/guardians of children present at the local health centre with the baby to receive oral (in Portuguese Creole) and written (in Portuguese) explanation about the study from the physician and to give consent for participation. The children belonging to arm I of the study will receive vaccination with the standard-titre EZ vaccine. At each visit to the health centre a physician will perform a medical examination. If the child is so ill that it needs to be hospitalised, it will only be able to participate in the study after it has recovered.

#### *Additional procedures, proposed immunological study*

In the proposed study it is planned to perform the first blood sample on the first contact at the health centre at 4½ months of age. At this age, all the children have received the third dose of DTP. On the same occasion, participants in arm I will receive a measles vaccine. Six weeks after this occasion (at 6 months of age), a blood sample will be obtained at home. Children enrolled in the immunological study will be included in a morbidity study to be able to assess the possible correlation between differences in cytokine profile and morbidity.

#### *Immunological analyses*

The project provides a unique opportunity to perform detailed immunological analyses in a vaccination trial in a resource-poor developing country in a manner that will not be technically demanding nor taxing for the study population. Considering the limitation of only measuring a Th1 marker (IFN- $\gamma$ ) in the face of growing evidence that a balance not only between Th1 and Th2 responses but also pro and anti-inflammatory networks are crucial for beneficial outcome of diseases and most probably vaccines, we will also measure IL-5, IL-13 as Th2, IL-10 as anti-inflammatory and TNF- $\alpha$  and IL-1 as pro inflammatory markers. With the advent of the multiplexed particle-based flow cytometric assays for simultaneous measurements of cytokines or antibodies in small volumes of biological samples it is now possible to conduct immuno-epidemiological studies without compromising the population sample size. This assay has been optimised for use in our setting, and is currently being used in Bissau in collaboration with Leiden University Medical Centre, The Netherlands. All blood samples will be collected by finger-prick in microtubes. Each participant to be blood sampled will have a blood smear prepared and examined for malaria parasitaemia. Participants with malaria will be treated according to local recommendations.

#### *Whole blood culture*

The blood will be diluted 1:10 with RPMI-1640 medium and cultured in 96 well round bottomed plates. Stimulations will besides from control medium be performed with mitogens: PHA, anti-CD3+anti-CD28, and LPS. PHA is a strong stimulus for T cell derived cytokines particularly for IFN- $\gamma$ , IL-13 and IL-5. Anti CD3+CD28 is a strong stimulus for stimulating IL-10 production from T cells whereas LPS will provide us with information on responsiveness of the innate immune system mediated via Toll Like Receptor 4. Furthermore, the following antigens will be used: PPD and TT. Supernatants will be collected on days 1 and 3 and frozen at minus 80 degrees until use.

#### *Cytokine determinations*

The representative cytokines of the Th1, Th2 and regulatory T-cells will be measured simultaneously in the multiplexed particle-based flow cytometric assays. This newly developed assay system which in theory would allow the detection of more than 50 different cytokines in a

small volume of 20 ul, is now operational at a level which allows the determination of now up to 8 cytokines simultaneously. The assay employs beads that are dyed with two fluorophores at varying ratios; different ratios therefore distinguish the test bead sets. Specific capture antibodies are coupled to specific bead sets and the different bead sets can be mixed together which means different cytokine capture antibodies can be added to the same sample. This refinement on the cytokine detection technology is of particular importance to immuno-epidemiological studies where volume of blood is a serious limiting factor.

#### *Antibody determinations*

Measles antibodies will be analysed at the Medical Research Laboratories in The Gambia by haemagglutination inhibition test (HAI), which has been in routine use for many years in The Gambia.

#### *Morbidity survey*

The children enrolled in the immunological study will be followed with morbidity visits between 4½ and 9 months of age to assess disease episodes, consultations and vaccine adverse events. The morbidity survey collects information on diarrhoea, upper and lower respiratory tract infections, abnormalities of the skin, the general well-being of the child including measurement of temperature, consultations and hospitalisations. Within the first two weeks after vaccination the child will be visited 5 times, thereafter once per week. In case of diarrhoea, a faecal specimen will be collected and analysed for parasites and rotavirus. In case of fever (an axillary temperature  $\geq 37.5^{\circ}\text{C}$ ), a blood smear will be collected for determination of malaria parasitaemia. In case of lower respiratory infection or other signs of severe disease, the mother will be urged to consult at the local health centre.

Further, the BHP monitors consultations at the local health centres and hospitalisations at the one paediatric department in Bissau. From these registers additional information on the children will be added.

#### *HIV-infection in Bissau*

The population in the study area has a high prevalence of HIV-2 infection (6-9%). However, very few children get HIV-2 infected and HIV-2 is therefore not expected to be an important confounder in the proposed studies. The prevalence of HIV-1 was 2.5% in the last survey before the war and is probably around 3-4 % at the moment among women of fertile age. Since the epidemic is recent, most mothers will be in the early phase of infection and vertical transmission is therefore expected to be somewhat lower than in other regions, presumably around 25%. We may ask for permission to carry out anonymous testing of blood samples that might be available from children who died to assess whether there is any indication of a differential effect for HIV-infected and uninfected children. Such permission has been granted in previous studies in Bissau.

#### *Sample size*

##### *Morbidity*

With an expected diarrhea frequency of 6 episodes per year for children under 3 years (36), we can assume that each child will have at least one episode of diarrhea or fever between 4 ½ and 9 months of age. With 200 vaccinated and 200 unvaccinated children followed for morbidity, we will with a power of 80% be able to find a 20% reduction in infection incidence.

Preliminary results indicate a 50% reduction in hospitalization rates for measles vaccination at 4 ½ months (table). Not only those who have taken the blood test, but all children (n = 5,755) included in the study will be registered in terms of hospitalizations. One third of the children enrolled at 4 ½

months will receive measles vaccine immediately, and 2/3 will receive measles vaccine at 9 months of age. With 765 vaccinated at 4 ½ months and 1,530 unvaccinated (who will receive the vaccine at 9 months) we will be able to find a 50% reduction in hospitalization with 80% power.

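### The 50% hospitalisation target comes from 2,022 children of this same trial, who then stay unseparated among the 5,755, so the pooled estimate is not an independent test of it

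*Protocol*

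**What the plan says.** Under Sample size, Morbidity, the protocol gives the source of its effect size: "Preliminary results indicate a 50% reduction in hospitalization rates for measles vaccination at 4 ½ months (table". It then says that "all children (n = 5,755) included in the study will be registered in terms of hospitalizations", not only those with blood samples. The power statement follows: "With 765 vaccinated at 4 ½ months and 1,530 unvaccinated" children, "we will be able to find a 50% reduction in hospitalization with 80% power". The control risk, significance level, sidedness and type of hospitalisation are not given there, and nothing says which children make up the 765 and 1,530.

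The table in question is under Measles vaccination trial, Preliminary results. It compares the arms of the same ongoing trial: 677 children vaccinated at 4½ months and 1,345 not. For non-measles admissions the overall RR and interval are "0.53 (0.26-0.99"). The same section reports: "The study was initiated in August 2003, and has currently recruited 2025 children".

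The trial aims listed in that section name antibody response, protection against measles and child survival, as well as reversal of the DTP effect. Hospitalisation is not named among them. It enters in the text introducing the table, as a morbidity outcome used because it is too early to judge mortality.

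**The concern.** The table includes nearly everyone recruited when the protocol was written (2,022 of 2,025), and its non-measles result is already nominally significant. If those children are pooled with later ones, and the result is read against the 50% target, part of the apparent agreement is the observation that set the target.

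The protocol already describes the table as supporting earlier work: "These preliminary results from a randomised trial corroborate our previous observational studies". A later pooled result could be read as one more independent corroboration although it contains the same admissions. What is at stake is how the final hospitalisation result is interpreted, not the validity of the randomised comparison.

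**Working it through.** **1. The plan's own figure.** With k = 2 controls per vaccinated child, p1 = p0/2 and p̄ = (p1 + 2·p0)/3:

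n1 = [zα·√(1.5·p̄(1−p̄)) + zβ·√(p1(1−p1) + p0(1−p0)/2)]² / (p0−p1)²

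The protocol gives no p0, level or sidedness, so these are assumptions (80% power, level 0.05):

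| Control risk p0 | Two-sided | Two-sided, continuity-corrected | One-sided |
|---|---|---|---|
| 5% | 707 | **765** | 552 |
| 4.83% (all admissions, 65/1,345) | 732 | 793 | 572 |
| 3.64% (non-measles, 49/1,345) | 981 | 1,061 | **766** |

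So 765 can be reached, but by two routes that imply different outcomes. At the non-measles risk with a two-sided test, 765 vs 1,530 has about 69% power.

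**2. The data already seen.** Non-measles: 13/677 = 1.92% vs 49/1,345 = 3.64%, so RR = 0.527. This is the row that matches a reduction of about 50%. Pooled risk = 62/2,022 = 3.07%.

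z = (0.0364 − 0.0192) / √[0.0307·0.9693·(1/677 + 1/1,345)] = 2.12, two-sided p = 0.034.

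**3. Overlap.** 677 + 1,345 = 2,022, and 2,022/5,755 = 35%. At 1:2 allocation, 5,755 splits into 1,918 and 3,837. Removing the table's children leaves 1,918 − 677 = 1,241 and 3,837 − 1,345 = 2,492, together 3,733.

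**4. Pooled test given the seen data, with no effect in later children.** With f the share of information already seen:

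P = 1 − Φ[(1.96 − √f·2.12)/√(1−f)]

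- f = 0.351: (1.96 − 0.593·2.12)/0.805 = 0.87, so P = 19%.
- Simulation (400,000 runs, seen counts held fixed): 18% at a 3.64% risk in later children, 19% at 3.07%.

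**5. If follow-up of the table's children is incomplete.** The table covers 4½ to 9 months of age, a window of 4.5 months. Assume even enrolment over 12 to 16 months before the table. Then 2,022·4.5/16 = 569 to 2,022·4.5/12 = 758 children were still in the window. Counting half of their follow-up as unseen gives f = (2,022 − 284)/5,755 = 0.302 to (2,022 − 379)/5,755 = 0.285, and P = 17% to 16%.

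**6. Power in the later children alone.** For 1,241 vs 2,492 and a 50% reduction, two-sided 0.05: about 89% at a control risk of 3.64%, and about 83% at 3.07% (formula and simulation agree within one percentage point).

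**The case against.** The strongest reply has four parts.

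*The final test keeps its level.* One analysis of all randomised children, carried out whatever the look showed, has its nominal 5% error rate. The 18-19% is conditional on favourable data already seen, and any trial with a favourable interim result shows such a rise. This is correct as statistics, so the figure must not be read as an inflated type I error. As a defence it needs a hospitalisation comparison planned before the look, and this document does not show one: the listed aims do not name hospitalisation, and it appears together with the favourable result.

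*The table did not create the hypothesis.* This stands. Reversal of the DTP effect is a listed trial aim, and the text cites earlier observational studies. A reader might infer that the hypothesis was both generated and tested on the same children; the documents support only that the size of the hospitalisation effect came from them.

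*No independent confirmation is claimed.* This also stands. The protocol never calls the comparison confirmatory, although it does give it a formal 80% power claim.

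*The overlap in the 765/1,530 comparison is not stated.* A reader might assume that these numbers are cumulative. Then 2,022 of 2,295 (88%) would already be seen, only 88 + 185 = 273 would be new, and the conditional chance would be 54-58%. The protocol does not say this. The numbers may be a required minimum or refer to later children, and that chance also assumes completed follow-up. The silence is worth correcting, but the 54-58% cannot be attributed to the plan.

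**Conclusion.** The concern holds in a limited form. The target effect comes from 2,022 children of the same trial, who make up 35% of the 5,755 to be registered for hospitalisation, and nothing separates them from later children. The pooled estimate is thus not an independent test of a 50% reduction. Conditional on the seen result, it would favour the vaccine significantly about 18-19% of the time with no effect in later children, or about 16-17% with some follow-up outstanding.

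These figures assume the non-measles outcome, a two-sided 0.05 test, a risk of 3.1-3.6% in later children, and use of all 5,755, which is the natural reading but not spelled out. If all admissions count, the table gives 13/677 vs 65/1,345, RR 0.40, assuming no child is in both rows. A null effect in later children is then hard to believe, given 0 vs 16 measles admissions, so these conditional figures should not be carried over to that outcome.

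A reader might conclude that the trial cannot confirm the effect at all. It can: the roughly 3,733 later children alone give about 83-89% power, above the 80% the plan asks for.

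**What to change.** Amend the hospitalisation paragraph under Sample size, Morbidity:

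- Keep the comparison of all randomised children.
- Specify that the estimate in children enrolled after the preliminary table (about 1,241 vs 2,492) is reported beside it as the independent test of the 50% reduction.
- Label the pooled estimate as including the data that set the target.
- State whether 765 and 1,530 count only children enrolled after the table.
- State whether the outcome is non-measles or all hospitalisation, with the control risk, level and sidedness behind the 765.

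The cost is a few sentences and one extra analysis of data that will be registered anyway. The later-children estimate is less precise. At a 3.64% control risk and RR 0.5, the standard error of log RR is √(1/22.6 − 1/1,241 + 1/90.8 − 1/2,492) = 0.23, against √(1/34.9 − 1/1,918 + 1/139.8 − 1/3,837) = 0.19 for all children. No further recruitment is needed.

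### The hospitalisation outcome is powered on a non-measles effect but named without excluding measles, so specific measles protection could count as the non-specific effect

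*Protocol*

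**What the plan says.** The general objective is "To investigate the immunological background for the non-specific effects" of DTP and measles vaccines (Objectives). Under Measles vaccination trial, the protocol explains that the hospital register "allows us to use hospitalisations as a morbidity outcome". The table that follows gives measles and non-measles admissions in separate rows, by sex. The all-children non-measles row has RR "0.53 (0.26-0.99").

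Sample size, Morbidity, then reads: "Preliminary results indicate a 50% reduction in hospitalization rates for measles vaccination at 4 ½ months (table"). It adds that "all children (n = 5,755) included in the study will be registered in terms of hospitalizations", and concludes: "With 765 vaccinated at 4 ½ months and 1,530 unvaccinated" (the latter to be vaccinated at 9 months) "we will be able to find a 50% reduction in hospitalization with 80% power". Neither the control rate nor alpha is given. The word for the outcome carries no qualifier.

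The Morbidity survey section describes visits "to assess disease episodes, consultations and vaccine adverse events", and the Analysis section plans to relate cytokine differences to differences in morbidity from 4½ to 9 months. Neither excludes measles or counts it separately. In the trial schedule, only arm I receives measles vaccine before 9 months.

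**The concern.** The effect size and the outcome it is attached to do not match. The 50% describes non-measles admissions; the powered outcome, as worded, is any admission. One group is vaccinated against measles during the outcome window and the other is not, so measles illness falls almost wholly on the controls. An outcome that includes measles mixes the vaccine's known specific protection with the non-specific effect the study is designed to explain, and a difference on it could not be assigned to either. The sex contrast, which is central to the protocol's hypothesis, would be affected as well, because measles makes up a larger share of admissions in control boys than in control girls.

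**Working it through.** **Inputs** (preliminary hospitalisation table, Protocol)

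| | EZ at 4½ months | No vaccine at 4½ months |
|---|---|---|
| Measles, all | 0/677 | 16/1,345 |
| Non-measles, all | 13/677 | 49/1,345 |
| Measles, male; female | 0/333; 0/344 | 10/698; 6/647 |
| Non-measles, male; female | 8/333; 5/344 | 20/698; 29/647 |

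Assumptions: no child is in both rows; alpha is 0.05, tried one- and two-sided because it is not stated.

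**1. Which row gives the 50%?**
- Non-measles: (13/677)/(49/1,345) = 0.0192/0.0364 = 0.53, a 47% reduction.
- Both rows: (13/677)/(65/1,345) = 0.0192/0.0483 = 0.40, a 60% reduction.

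The 50% is the non-measles figure.

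**2. Reproducing 765:1,530.** Two proportions, 1:2 allocation, RR 0.50, 80% power. Vaccinated children needed:

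| Control rate | Test | Uncorrected | Continuity-corrected |
|---|---|---|---|
| 5% (round figure) | two-sided | 707 | 765 |
| 4.83% (both rows) | two-sided | 732 | 793 |
| 3.64% (non-measles) | two-sided | 981 | 1,061 |
| 3.64% (non-measles) | one-sided | 766 | 847 |

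The stated number fits a round 5% with a two-sided test, or the non-measles rate with a one-sided test. It does not settle which outcome was meant.

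**3. Power for the non-measles outcome.** Power = Φ[(p2 − p1 − z·SE0)/SE1], where SE0 = √[p̄(1 − p̄)(1/n1 + 1/n2)], SE1 = √[p1(1 − p1)/n1 + p2(1 − p2)/n2], and p̄ is the pooled rate. Here p2 = 0.03643 and p1 = 0.01822.
- 765:1,530: SE0 = 0.00760, SE1 = 0.00681. Two-sided: (0.01822 − 1.96 × 0.00760)/0.00681 = 0.49, power 68.7%. One-sided (z = 1.645): 0.84, power 80%.
- All 5,755, about 1,918:3,837: SE0 = 0.00480, SE1 = 0.00430. Two-sided: (0.01822 − 1.96 × 0.00480)/0.00430 = 2.05, power about 98%.

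For comparison, the combined rate of 4.83% gives 81.9% at 765:1,530, two-sided.

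**4. What pooling would do with no non-specific effect.** Assume complete measles protection and the same non-measles rate in both groups.
- RR = 49/65 = 0.75, an apparent 25% reduction.
- Difference: 0.04833 − 0.03643 = 0.01190.
- Chance of a significant result, two-sided 5%: at 765:1,530, (0.01190 − 1.96 × 0.00912)/0.00871 = −0.69, about 25%. With 5,755 children, (0.01190 − 1.96 × 0.00576)/0.00550 = 0.11, about 54%.

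The larger sample makes the misattribution more likely.

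**5. Sex contrast.**
- Boys: non-measles RR (8/333)/(20/698) = 0.84; both rows (8/333)/(30/698) = 0.56.
- Girls: non-measles RR (5/344)/(29/647) = 0.32; both rows (5/344)/(35/647) = 0.27.

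Measles is 10 of 30 admissions in control boys and 6 of 35 in control girls, so pooling shifts the boys' estimate most.

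**6. The 200 v 200 substudy.** At the table's rate, 200 × 16/1,345 = about 2.4 measles admissions would be expected in 200 controls. Measles cases not admitted are not given, so the effect on the survey or the cytokine comparison cannot be calculated.

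**The case against.** The strongest reply is that the protocol nowhere says measles will be pooled, and its practice points the other way: the table separates the two causes, the text discusses them separately, and the power paragraph refers back to that table. Outcome wording is also often refined in an analysis plan, which is not shown here. Much of this stands, and it rules out several stronger readings a reader might infer:

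- That the planned outcomes definitely include measles. This would be an inference from silence.
- That the quoted 50% is inflated by measles. It is not; it matches the non-measles row.
- That 765:1,530 proves a measles-inclusive outcome. A one-sided test on the non-measles rate gives 766.
- That the survey or cytokine results will be materially distorted. The expected number of measles admissions there is small, and the Analysis section calls the work explorative.

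What the reply does not answer is the mismatch inside the protocol's own power statement. An effect taken from one outcome is attached to the name of a broader one. That is stated in this document, not deferred to another, and an analyst following the wording would count measles admissions.

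**Conclusion.** The point holds as a mismatch between effect size and outcome name, left open in a way that would mislead if followed literally. Pooling would produce RR about 0.75 with no non-specific effect, and would move the boys' RR from 0.84 to 0.56 and the girls' from 0.32 to 0.27. Once the outcome is named as non-measles, the claimed 80% power at 765:1,530 holds only for a one-sided 5% test; two-sided it is about 69%. Using all 5,755 children restores it to about 98%.

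These figures assume that no child is in both rows, that the two tabulated categories are the admissions of interest, that the preliminary control rates carry over to the full trial, and that alpha is 0.05. For the morbidity survey and cytokines the concern is one of principle only; its size cannot be derived from the document.

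**What to change.** 1. In Sample size, Morbidity, name the outcome as non-measles hospitalisation. Keep measles hospitalisation as a separate specific-effect outcome, as the table already does.
2. Restate the power for that outcome, giving the control rate, alpha and sidedness, and say whether the analysis uses 765:1,530 or all 5,755 children.
3. In the Morbidity survey and Analysis sections, report measles episodes separately. Add a sensitivity analysis of the morbidity and cytokine comparisons that leaves out children with clinically identified measles in either group. It should remain a sensitivity analysis, because the exclusion is made after randomisation and will fall mostly on controls.
4. Do not exclude controls on a rise in HAI titre. Vaccination itself raises titres, so the exclusion could not be mirrored in the vaccinated group.

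The cost is mainly wording. The hospitalisation split already exists in the table, but the survey items listed do not include a measles diagnosis, so the protocol must say how clinical measles is identified there. About a quarter of control admissions (16 of 65) leave the main outcome, and the stated power at 765:1,530 becomes less favourable.
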